# Implementation of integrated care for type 2 diabetes Mellitus and Periodontitis in Germany: study protocol for a practice-based and cluster-randomized trial

**DOI:** 10.1186/s12903-024-04672-1

**Published:** 2024-08-02

**Keywords:** Screening, Periodontitis, Diabetes, Integration, Implementation, Germany, General practice, Dental practice, Oral health

## Abstract

**Background:**

Type 2 Diabetes mellitus (T2DM) and periodontitis share common risk factors and influence one another. However, primary care and oral health care continue to operate separate from each other and fail to synchronize care for patients with T2DM and periodontitis. The purpose of this practice-based trial is to evaluate the implementation of a new integrated care pathway for patients with T2DM and periodontitis. The new approach integrates a screening for T2DM risk in dental care settings in patients with periodontitis, a screening for periodontitis risk in primary care settings in patients with T2DM, and mutual referrals between dentists and primary care physicians.

**Methods:**

Two practice-based studies will be carried out in parallel: (i) In dental care settings: a practice-based, multi-centric, cluster-randomized, controlled trial with a control and an intervention group; (ii) in primary care settings: a practice-based, multi-centric, non-randomized, controlled trial with a synthetic control group calculated from claims data. Following a two-step recruitment approach, 166 dentists and 248 general practitioners will be recruited, who themselves will recruit a total of 3808 patients in their practices. Patient data will be collected at baseline, 12 months, and 24 months after study enrollment. The evaluation comprises: (i) impact evaluation, using a hierarchical linear mixed model; (ii) process evaluation, based on surveys alongside the trials; (iii) economic evaluation. In addition, a Discrete-Choice-Experiment will identify provider’s payment preferences for the new care approach.

**Discussion:**

Upon successful implementation, the intervention will enable health care providers to detect a risk for T2DM and periodontitis in patients at an early stage, thus providing patients an opportunity for timely diagnosis and therapy. Ultimately, this can lead to increased quality of life and reduced health care expenditures. On a methodologic level, the project provides novel insights into a complex intervention on the intersection of general practice and dental care.

**Trial registration:**

The study was prospectively registered at the German Clinical Trials Register (https://drks.de/search/de/trial/DRKS00030587) on 3. July 2023 under ID “DRKS00030587“.

**Supplementary Information:**

The online version contains supplementary material available at 10.1186/s12903-024-04672-1.

**Table Taba:** 

Contributions to the literature	
- First large-scale practice-based trial on the implementation of integrated care for type 2 diabetes mellitus and periodontitis in both the primary medical care and the dental care settings. - Novel methodological approach to evaluate implementation of integrated care pathways in previously asynchronous care settings (dentistry and primary care). - Unique comparison of similarities and differences between physicians and dentists with respect to barriers and facilitators for implementation of interprofessional care integration. - Identification of provider’s payment preferences as integral component for implementation. - Unique insights into feasibility of implementation research in dental practice settings.	

## Background

The 2021 WHO Resolution on Oral Health resolution emphasizes the need for better integration of oral health and primary health care [1].

Previous evidence suggests that oral diseases and other noncommunicable diseases occur in parallel [2, 3]. Periodontitis is 2–3 times more prevalent in patients suffering from type-2 diabetes mellitus (T2DM) [4]. T2DM-patients have a higher periodontitis risk [5–7]. Among T2DM patients, periodontitis therapy was shown to reduce HbA1c by 0.6%-points up to 12 months [8] as well as healthcare costs [9, 10]. On the other hand, glycemic control in periodontitis patients may be improved by periodontitis therapy [7, 11, 12].

This shows that better integration of T2DM and periodontitis care offers potential to reduce disease burden and costs - yet, the diagnosis and treatment of T2DM and periodontitis are still disintegrated in Germany, which is the context for this study [13]. The number of undiagnosed T2DM-cases amounts to around 2 million and it takes an average 8 years until T2DM is diagnosed [14]. There is also a discrepancy between need and utilization of periodontitis care: While 10 million people suffer from severe periodontitis, there are 1 million reimbursed treatment cases per year [15]. These gaps between need and utilization give raise to avoidable disease burden and costs. To this end, the present paper describes the protocol for practice-based studies on integrated T2DM and periodontitis care in Germany.

### Description of the implementation approach for integrated care

The **Dig**itally **In**tegrated T**2**DM and **Perio**dontitis (DigIn2Perio) study aims to evaluate new interprofessional care pathways as an implementation strategy to achieve integrated care for T2DM and periodontitis. The care pathways include (different from usual care):

T2DM screening among periodontitis patients, using the FINDRISK-questionnaire [16, 17].Periodontitis screening among T2DM patients, using the periodontitis risk score of the German Society for Periodontology [18].Tailored patient information about the interplay between T2DM and periodontitis.Mutual referrals between primary care physicians and dental practitioners.Digitally supported data capture and exchange via the German Telematics Infrastructure [19].

Figure 1 gives an overview of the implementation approach for integrated care:

**Fig. 1 Fig1:**
[figure not shown]
Intervention concept: (**a**) initiation in dental practice; (**b**) initiation in primary care practice

### Research questions

#### Primary question

Does the new approach for implementation of integrated T2DM and periodontitis care result in:

(i)lowered HbA1c among T2DM patients;(ii)additional T2DM diagnoses among periodontitis patients?

#### Secondary questions

Does the new approach for implementation of integrated T2DM and periodontitis care:

lead to better periodontal health in response to dentist-initiated T2DM care?improve patients’ quality of life?lead to more risk-tailored utilization of care and medication?lend itself for practice implementation as anticipated? (process evaluation)provide good value-for-money?evoke specific provider payment preferences?

## Materials & methods

### Endpoints

#### Primary endpoints

##### In general practitioner (GP) practices

HbA1c reduction among patients in the T2DM Disease Management Program (T2DM-DMP) who had not received periodontitis therapy within the past 12 months. Recorded by medical assistants at: T0 (recruitment); T1 (after 12 months); T2 (after max. 24 months). [primary data]

##### In dental practices

New T2DM diagnoses among periodontitis patients who had not been diagnosed with a diabetes condition before. Recorded by dental assistants at T1 (after 12 months). [primary data]

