##### In dental practices

% of teeth with pocket probing depth > 4 mm and bleeding on probing (BOP) [primary data].T2DM medication (no medication, oral medication, insulin injections) [primary data].Patients’ quality of life [primary data].Utilization of T2DM care (blood sugar-parameters, inclusion in T2DM-DMP) [primary data].Utilization of periodontal care [claims data].

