###### Dentist study

Sample size calculation refers to the primary endpoint and is therefore based on a Z-Test with non-pooled variance. We assume that, compared to the control group, the rate of new diabetes diagnoses will be 0.1 in the intervention group during the next 4 quarters [22]. For the control group we assume a rate of 0.05 (calculated from an internal analysis of insurer-data for the areas the study will be performed in). It is therefore assumed that the intervention allows for an additional 5% of diabetes diagnoses. Sample size is calculated with α = 5% and power = 80%. Patients are clustered in practices, so an intra-class-correlation of 0.03 and a cluster size of 8 patients per practice is assumed. Assuming an allocation ratio of 1:1 for control vs. intervention group, this results in a sample size of 528 patients (66 practices, 8 patients each) per group. With an assumed drop-out rate of 20%, sample size in each group will be 664 patients (83 practices, 8 patients each), adding up to a total of 1328 patients in 166 practices. Sample size calculation was performed using PASS v16.0.3.

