##### Baseline survey (T0)

Patients in both studies receive a written questionnaire on sociodemographic data and a self-disclosure of medical conditions. The questionnaire further contains a question on current, subjective health, translated from the publicly available, validated Short Form 36 (SF-36)-questionnaire by RAND Corporation [23]. Additionally, the questionnaire contains the respective questions for periodontitis/T2DM risk assessment (in the dentist study, this is only the case for the intervention group), so patients may calculate their risk score. The medical/dental assistant will be available for questions during this process. The further course differs depending on the study and risk-score.

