**Fig. 3 Fig3:**
[figure not shown]
Baseline survey T0 in dental practices

After T0, all patients receive usual care. During the following, regular dentist appointments, the dentist will approach high-risk patients in the intervention group regarding the GP appointment and potential measures that the GP took. The follow-up survey T1 will take place 12 months after recruitment.

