##### Survey T1 (first follow-up)

The medical assistant in the general practice identifies all participating patients during a regular DMP-appointment. In the dental practice, the dental assistant identifies all participating patients during a regular appointment. Patients are asked to fill out another written questionnaire on their health and a potential periodontitis/T2DM diagnosis and therapy. Subjective health is once again assessed using the first question of the SF-36. To allow for a comparison with the patient’s subjective health at T0, question 2 of the SF-36 will be asked as well.

In the GP-study, the GP asks the patients about their potential periodontitis diagnosis and/or therapy. The primary endpoint measured during the regular DMP-appointment as well as the questionnaire data (including secondary endpoints) for T1 will be transferred to the research database by the medical assistant.

In the dentist study, the dentist in both control and intervention group asks the patients about their potential T2DM diagnosis and/or therapy. The current periodontal status and the periodontal services provided will, together with the questionnaire data, be transferred to the research database by the dental assistant.

The second, and final, follow-up survey takes place 6 to 12 months after T1, depending on when the patient was recruited for T0.

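### The dental primary endpoint rests on patient report to staff who know their arm, and no planned sensitivity analysis separates additional diagnoses from additional reporting

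*Protocol article*

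**What the plan says.** Under Primary endpoints, In dental practices, the endpoint is "New T2DM diagnoses among periodontitis patients who had not been diagnosed with a diabetes condition before", and it is "Recorded by dental assistants at T1 (after 12 months). [primary data". Two GP endpoints carry a combined primary and claims tag, and one dental secondary endpoint carries a claims tag; this one carries the primary-data tag alone.

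Survey T1 (first follow-up) describes how the information arises. First, "Patients are asked to fill out another written questionnaire on their health and a potential periodontitis/T2DM diagnosis and therapy". Second, "the dentist in both control and intervention group asks the patients about their potential T2DM diagnosis and/or therapy". The dental assistant transfers the data to the research database. The text shown describes no laboratory, GP or claims confirmation.

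Randomization is by practice (Randomization procedure, Dentist study). The practice's own assistant recruits and collects the data (Recruitment).

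Two contacts differ by arm before T1:
- The baseline questionnaire contains the risk-score questions, but "in the dentist study, this is only the case for the intervention group" (Baseline survey (T0)).
- At regular appointments after T0, "the dentist will approach high-risk patients in the intervention group regarding the GP appointment and potential measures that the GP took" (T0 in dental practices).

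For planning, the control rate of 0.05 was "calculated from an internal analysis of insurer-data for the areas the study will be performed in" (Sample size calculation, Dentist study). The intervention rate of 0.10 comes from a cited source. The only dental endpoint tagged with claims data is "Utilization of periodontal care [claims data".

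**The concern.** A patient-reported diagnosis is sound for comparing arms only if true diagnoses are captured, and false ones excluded, equally well in both. Here the patient who answers at T1 has been handled differently by arm. An intervention patient has answered diabetes risk questions and, if at high risk, has been asked about the GP appointment and its consequences. That patient may recall and report a diagnosis more completely than a control patient, or may report diabetes on the strength of a high risk score. Staff who delivered the screening and referral collect the answer.

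The same contacts are also the route by which the intervention should produce real diagnoses. With report alone, the analysis cannot tell the two apart, so a positive result would support more reported diagnoses but not necessarily more diagnoses.

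There is also a planning mismatch. The 0.05 comes from insurer data, whereas the analysed outcome is patient report. If report captures fewer events than coding does, both recorded rates fall below their planning values and power is lost even without any difference between arms.

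**Working it through.** **Inputs from Sample size calculation, Dentist study:** rates 0.10 and 0.05, α = 5%, power 80%, unpooled Z-test, ICC 0.03, 8 patients per practice, 1:1 allocation, 20% drop-out. The test is two-sided (Statistical hypotheses and analyses, Dentist study).

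**Reproducing the plan's figure**
- n per arm = (1.960 + 0.842)² × (0.10 × 0.90 + 0.05 × 0.95) / 0.05² = 431.7
- Design effect = 1 + (8 − 1) × 0.03 = 1.21; 431.7 × 1.21 = 522.3, or 65.3 practices, rounded up to 66 practices = 528 patients
- Drop-out: 528 / 0.8 = 660, or 82.5 practices, rounded up to 83 practices = 664 patients

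Both stated figures reproduce. The sample size arithmetic is not at issue.

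**Set-up for the illustration.** Effective size per arm = 528 / 1.21 = 436. For recorded rates a and b, SE = √[(a(1 − a) + b(1 − b)) / 436], and the rejection probability is Φ(d/SE − 1.96) + Φ(−d/SE − 1.96) with d = a − b. This is the planning test, used as an approximation to the logistic mixed model. With 0.10 against 0.05, SE = 0.01775, d/SE = 2.82 and power = 80.4%, as planned.

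**No true effect (5% in both arms), unequal reporting (assumed)**

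| Assumption | Recorded rates | Rejection probability |
|---|---|---|
| Equal, complete reporting | 5% vs 5% | 5.0% |
| 95% vs 80% of diagnoses captured | 4.75% vs 4% | 8.4% |
| 1% false-positive reports, intervention arm only | 5.95% vs 5% | 9.5% |
| 100% vs 80% captured | 5% vs 4% | 11.0% |
| 2% false-positive reports, intervention arm only | 6.9% vs 5% | 22.1% |
| 100% vs 60% captured | 5% vs 3% | 32.6% |

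For the 5% vs 4% row: SE = √[(0.0475 + 0.0384) / 436] = 0.01403, d/SE = 0.713, and Φ(−1.247) + Φ(−2.673) = 0.106 + 0.004 = 0.110. In patients, one percentage point of 528 is about 5 people.

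**True rates 10% vs 5%, equal under-reporting (assumed)**
- 90% captured in both arms: 9% vs 4.5%, power 75.8%
- 80% captured in both arms: 8% vs 4%, SE = √[(0.0736 + 0.0384) / 436] = 0.01602, d/SE = 2.50, power 70.4%

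**What the planned sensitivity analyses cover.** The dentist-study analysis section lists checks of the missing-data assumptions, a possible alternative way of handling missing data, and subgroup analyses by state and insurance status. None varies the definition or source of the outcome, so none responds to misreporting.

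**The case against.** The strongest reply is that capture at T1 is symmetric: the same written questionnaire and the same enquiry by the dentist are used in both arms, and the endpoint is recorded then, not at the interim contacts. The interim contact follows up the referral and so belongs to the pathway under test; more true diagnoses are its intended effect. All of this stands. A reader might infer that control patients are asked less at T1, or that the interim contact is purely a source of bias. The article supports neither. What remains is that identical questions need not be answered alike after different preparation.

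A second reply is that corroborating data exist. The dental secondary endpoints include T2DM medication, blood-sugar parameters and inclusion in the T2DM-DMP. This also stands, with the limit that these items are primary data and may themselves be patient-reported. They make a check possible, but the article does not plan one.

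Third, claims may not be able to replace the endpoint. Eligibility covers any statutory insurer, the GP-study text contrasts cross-insurer DMP data with data from a single insurer, and claims in the dentist study are named only for periodontal care. No linkage of diabetes claims for dental patients is described. A reader might infer that a claims-based primary endpoint is readily available, or that both planning rates came from claims. The article shows neither; only the 0.05 came from insurer data.

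Finally, a sensitivity definition is often left to the SAP, and Fig. 3 and the full protocol are not shown. A confirmation step may be described there. The point concerns what the article itself fixes: the source of the endpoint and a list of sensitivity analyses that does not address it.

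**Conclusion.** The concern holds as a limit on what a positive result can show. The primary endpoint is patient report, tagged as primary data only. The collecting staff must know their arm: the article does not say so outright, but they work in practices that either deliver the intervention or do not, and no blinding is described. What the patient has experienced before T1 differs by arm, and no planned analysis tests whether the effect survives a stricter outcome definition.

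The size cannot be established from the article, which gives no reporting rates. Under the assumed rates shown, a recorded difference of one percentage point arising from reporting alone roughly doubles the false-positive risk, from 5% to about 11%, and equal 80% capture costs about 10 points of power. These figures show sensitivity and are not estimates of the actual error rate. It would go too far to say that the result will be biased, or that the type I error is 11% or 33%. The sample size calculation is internally correct.

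**What to change.** Keep the primary endpoint and the sample size. Pre-specify one supportive sensitivity analysis, applied identically in both arms, with a stricter outcome:

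1. A reported new diagnosis corroborated by items already collected: T2DM medication, blood-sugar parameters or T2DM-DMP inclusion. State which item or combination counts. For blood sugar, use a result; the mere fact of testing would not corroborate, because referral itself may increase testing.
2. For patients whose claims are available, a claims-coded incident diabetes diagnosis between T0 and T1.

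Report these estimates with 95% confidence intervals beside the primary one. If the effect is not seen for corroborated diagnoses, word the conclusion as an effect on reported diagnoses. If a confirmation step already exists in the full protocol, it is enough to state it.

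Two additions are best avoided. Filling missing primary outcomes from claims would mix two definitions in an insurer-selected subset. A rule that the estimates must agree in size, without a margin, could fail by chance.

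The corroboration analysis costs SAP wording and one derived variable. The claims part depends on linkage that the article does not describe, covers only a subset of patients and arrives with a lag. The corroborating items may be partly patient-reported, and the stricter definition will miss some genuine diagnoses, lowering event counts and precision.

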#### Secondary endpoints

##### In GP practices

Utilization of periodontitis therapy (yes/no) [primary & claims data].T2DM medication (no medication, oral medication, insulin injections) [primary & claims data].Patients’ quality of life [primary data].

##### In dental practices

% of teeth with pocket probing depth > 4 mm and bleeding on probing (BOP) [primary data].T2DM medication (no medication, oral medication, insulin injections) [primary data].Patients’ quality of life [primary data].Utilization of T2DM care (blood sugar-parameters, inclusion in T2DM-DMP) [primary data].Utilization of periodontal care [claims data].

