##### Inclusion & exclusion criteria

Table 1 illustrates inclusion & exclusion criteria for practice personnel and patients alike in the main study.

**Table 1 Tab1:** Inclusion and exclusion criteria of the main study

	Practice & practice personnel	Patients
**Inclusion criteria**	- Legal age - Ability to consent	
	- Established, licensed physicians and assistants - Based in Baden-Wuerttemberg or North Rhine-Westphalia - Working computer system with internet connection - Patients physically visit the practice	- Insured with a statutory health insurer - GP-study: In T2DM-DMP in 4 of 5 past quarters - Dentist study: Need for systemic periodontitis therapy
**Exclusion criteria**	Persons who : - Live in a nursing home - Have a legal guardian - Are not of legal age - Are cognitively or linguistically incapable to participate	
	- Are not licensed as physician - Don’t practice in Baden-Württemberg or North Rhine-Westphalia	- Are not insured with a German statutory health insurer (or not entitled to care that exceeds basic health care coverage) - GP-study: a periodontitis therapy in the past 12 months - Not in the T2DM-DMP in 4 of 5 past quarters - Dentist study: Previously diagnosed with diabetes

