### Statistical hypotheses and analyses

#### General practitioner study

For the primary outcome, we will test the null hypothesis H_0_^HA^: µ_IG_^T1−T0^ = µ_KG_^T1−T0^ against the alternative hypothesis H_1_^HA^: µ_IG_^T1−T0^ ≠ µ_KG_^T1−T0^ on a two-sided significance-level of 5%. µ_IG_^T1−T0^ and µ_KG_^T1−T0^ represent the reduction of the HbA1c-parameter between baseline (T0) and after 4 quarters (T1) in both groups.

Evaluation of the intervention contains descriptive and explorative statistical analyses of gathered study data as well as available claims data. The goal is an independent, scientifically valid and differentiated statement on effectiveness of the intervention regarding a reduction of the HbA1c parameter using an intervention study with parallel control group. The control group will be calculated from insurer claims data as well as DMP-documentation data across insurers. Using their registration number, intervention practices will be removed from the control group data. Study data will be described using descriptive methods.

Primary analysis will be a hierarchical, linear mixed model representing the multi-level structure of the data (level 1: practice, level 2: patient). For the test of H_0_^HA^, the dependent variable will be “reduction of HbA1c between T0 and T1”. The model contains the practice as a random effect and HbA1c at baseline (T0), age, sex, insurance status, state and residential area as fixed effects on the patient level. Here, only variables that are also included in claims data can be used.

It can be assumed that claims data will be complete and missing values will only occur in the additional study data and the questionnaires. Missing values of the primary outcome will be imputed using multiple imputation [27] while accounting for the baseline-variables age, sex, insurance status and residential area. Assumptions on missing values will be analyzed and an alternative procedure to handle missing data, such as an analysis of the full dataset, will be looked into.

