#### Dentist study

For the primary outcome, we will test the null hypothesis H_0_^ZA^: π_IG_^T1−T0^ = π_KG_^T1−T0^ against the alternative hypothesis H_1_^ZA^: π_IG_^T1−T0^ ≠ π_KG_^T1−T0^ on a two-sided significance-level of 5%. π_IG_^T1−T0^ and π_KG_^T1−T0^ represent the rate of new diabetes diagnoses between baseline (T0) and after 12 months (T1) in both groups.

Primary analysis will be performed using a generalized, logistic mixed model adequately representing the multi-level structure of data (practice on level 1, patients on level 2). For the test of H_0_^ZA,^ the „rate of new diabetes diagnoses between T0 and T1” will be used as the dependent variable. The model contains the practice as a random effect and the group (intervention vs. control), age, sex, insurance status, state and residential area as fixed effects on the patient level.

It can be assumed that claims data will be complete and missing values will only occur in the additional study data and the questionnaires. Missing values of the primary outcome will be imputed using multiple imputation [27] while accounting for the baseline-variables age, sex, insurance status and residential area. To check for the sensitivity of results, assumptions on missing values will be analyzed and an alternative procedure to handle missing data, such as an analysis of the full dataset, will be looked into. Further sensitivity analyses include sub-group analyses for both states and for insurance status.

Secondary endpoints will be presented descriptively first. Where appropriate, secondary endpoints will be explored similar to the primary analysis. For binary endpoints, logistic regression analyses will be performed. For continuous endpoints, linear regression analyses will be performed. For all estimated effects we will present descriptive p-values and 95% confidence intervals. All analyses are performed using a validated R environment with R version 4.0.0 or higher. The primary analysis is independently counter-programmed in SAS version 9.4 or higher.

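### Dentist study: taken literally, the model for continuous secondary endpoints omits the T0 value of the outcome, which costs precision; teeth lost should be reported beside the periodontal score

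*Protocol article*

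**What the plan says.** Protocol article, Secondary questions: the first asks whether the new approach will "lead to better periodontal health in response to dentist-initiated T2DM care".

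Secondary endpoints, In dental practices: the measure for this is the percentage "of teeth with pocket probing depth > 4 mm and bleeding on probing (BOP) [primary data". The article does not state the denominator, how teeth lost after T0 are handled, or whether the follow-up value or the change is analysed. Quality of life is also listed as a secondary endpoint.

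Table 1: patients enter with "Dentist study: Need for systemic periodontitis therapy".

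Statistical hypotheses and analyses, Dentist study: "Where appropriate, secondary endpoints will be explored similar to the primary analysis". Also: "For continuous endpoints, linear regression analyses will be performed". The primary model referred to has a random practice effect and these fixed effects: "the group (intervention vs. control), age, sex, insurance status, state and residential area as fixed effects on the patient level". Secondary effects get descriptive p-values and 95% confidence intervals.

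General practitioner study, same section: the fixed effects there include "HbA1c at baseline (T0), age, sex, insurance status, state and residential area as fixed effects on the patient level".

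Data capture: the subjective health question is asked of all patients at T0 (Baseline survey). Transfer of periodontal status to the research database is described under Survey T1 and Survey T2. The T0 text does not mention it, and the figure with the T0 pathway is not shown.

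**The concern.** The covariate list of the dentist primary model suits a yes/no endpoint that every patient starts without. It does not suit a score that already differs between patients at entry. Everyone recruited needs periodontal therapy, but the extent of disease will vary, and a model without the T0 value leaves that variation in the residual. The single subjective health item has the same problem.

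The first secondary question rests on this comparison, and the signal is likely to be small. The plan assumes a diagnosis rate of 0.10 against 0.05. If the periodontal effect runs mainly through new diagnoses, it would arise in about 5% of patients, so precision should not be given away.

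A second issue concerns reading the score. Probing depth and bleeding can be recorded only on teeth that are present. An affected tooth that is extracted leaves both numerator and denominator, and the percentage falls although nothing has healed.

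**Working it through.** **1. The plan's own figure.** The article gives no sample size or precision for the periodontal endpoint, so the check starts from the dentist sample size.

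- Inputs (Sample size calculation, Dentist study): rates 0.10 and 0.05, two-sided alpha 5%, power 80%, unpooled Z-test, ICC 0.03, 8 patients per practice, 20% drop-out.
- n per group = (1.960 + 0.842)² × (0.10 × 0.90 + 0.05 × 0.95) / 0.05² = 431.7.
- Design effect = 1 + (8 − 1) × 0.03 = 1.21. Then 431.7 × 1.21 = 522.3, which rounds up to 66 practices × 8 = 528.
- Drop-out: 66 / 0.8 = 82.5, so 83 practices × 8 = 664 per group, 1328 in 166 practices.

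All stated figures are reproduced. They rest on the primary endpoint and do not change with this point.

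**2. Precision lost without the T0 value.** With T0 to follow-up correlation r, adjustment multiplies the residual variance by 1 − r². The detectable difference in SD units, with 528 per group and design effect 1.21, is (1.960 + 0.842) × √[(2 × 1.21 / 528) × (1 − r²)].

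| Assumed r | Variance removed (r²) | Detectable difference |
|---|---|---|
| no adjustment | 0% | 0.190 SD |
| 0.3 | 9% | 0.181 SD |
| 0.5 | 25% | 0.164 SD |
| 0.7 | 49% | 0.135 SD |

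The documents give no r. The ICC of 0.03 is carried over from the primary endpoint, and r is taken to act alike within and between practices.

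**3. Does omission leave a difference between arms?** The 95% range of the chance difference in baseline means, with 66 practices of 8 per arm, is ±1.96 × √(2 × DE / 528), where DE = 1 + 7 × ICC.

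- ICC 0.03: DE 1.21, ±0.13 SD.
- ICC 0.10 (assumed): DE 1.70, ±0.16 SD.
- ICC 0.20 (assumed): DE 2.40, ±0.19 SD.

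This difference is centred on zero.

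**4. Extraction.** With n teeth, d affected, k affected teeth extracted and no healing, the score on teeth present moves from d/n to (d − k)/(n − k). Take 24 teeth with 6 affected (assumed): 6/24 = 25.0%.

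- k = 1: 5/23 = 21.7%.
- k = 2: 4/22 = 18.2%.
- k = 3: 3/21 = 14.3%.

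The score falls by 3.3 to 10.7 percentage points. On the 24 teeth present at T0, with lost teeth counted as affected, it stays at 6/24 = 25.0%.

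**The case against.** **The baseline value is not expressly excluded.** The article says similar, and only where appropriate. It lists no covariates for the linear regressions, and the general practitioner model adjusts for baseline HbA1c, so the authors may intend the same here. A statistical analysis plan may settle it. This stands: a reader might infer that the plan analyses the periodontal score without its baseline, and no sentence says so. What remains is that the only covariate list the text points to is the wrong one for these endpoints.

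**Subjective health already has a baseline-based analysis.** The Economic evaluation section plans a difference-in-differences analysis of subjective health, and Survey T1 adds a question for comparison with T0. The first belongs to the economic evaluation, and the second is an extra question at follow-up. Neither puts the T0 value into the clinical secondary analysis.

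**Large baseline differences.** A reader might infer that these stay in the comparison between arms. The documents do not support that. Practices are randomized 1:1, and the large differences are between patients, where they act as noise.

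**Extraction.** A reader might infer that the score favours one arm. That needs different extraction rates. The documents give no rate and no mechanism: what differs is screening, information and referral, and all patients receive usual care after T0. The denominator is also unstated, so teeth present is the natural reading, not the stated rule. Counting every lost tooth as not healed in the main score would be a debatable composite. These points stand, and they limit the remedy to a supporting report.

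**Conclusion.** The point holds as a modest one. Taken literally, the reference to the primary analysis leaves the T0 value out of the models for the dentist study's continuous secondary endpoints. Including it would remove 9% to 49% of the residual variance for assumed correlations of 0.3 to 0.7. The detectable difference would fall from 0.190 SD to between 0.181 and 0.135 SD. Omission does not bias the comparison: the expected baseline difference between randomized arms is zero, with a 95% chance range of about ±0.13 to ±0.19 SD for ICCs of 0.03 to 0.20. That range covers chance only.

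The extraction effect is real arithmetic if the score uses the teeth present. It affects how a fall in the score should be read, and nothing in the documents shows that it differs by arm. The tooth counts, correlations and ICCs above 0.03 are assumptions. The endpoints are secondary with descriptive p-values, so the primary analysis and the sample size stand.

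**What to change.** 1. State that continuous secondary endpoints in the dentist study are modelled with the T0 value of the same measure as an added fixed effect. For subjective health the value is collected at T0 in both arms.
2. For the periodontal score, first confirm that T0 periodontal status is transferred to the research database. If it is not, add it. The covariate, the tooth-loss count and the sensitivity analysis below all depend on it.
3. Report the number of teeth lost since T0, by arm, beside the score.
4. Add a sensitivity analysis on the teeth present at T0, with lost teeth counted as affected. This also gives a value for a patient who has lost all teeth and would otherwise have no score.

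The cost is slightly more analysis work, plus one extra data transfer if T0 status is not yet captured. The sensitivity analysis will also count teeth lost for non-periodontal reasons as affected, which is why it supports the main score and does not replace it. No change to the sample size or the primary analysis is needed.
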